### Development versus validation

Data will be collected from patients, caregivers and clinicians during the validation
phase to compare patient-reported problem severity, that is, ‘felt’
need collected in validation phase only (as measured by the patient-reported IPOS)
and professional-reported problem severity, that is, ‘normative’ need
(as measured by the clinician-reported IPOS, phase of illness, AKPS), by reporting
correlation across levels of complexity and across conditions. We will assess how
professional-reported measures relate to patient-reported outcomes across different
levels of complexity (ie, in relation to casemix classes), in order to determine
optimal outcome measures and quality indicators.

We will compare data on resource use from two sources: (1) clinician-completed brief
PRUS, and (2) patients and family-completed CSRI, to better understand how the PRUS
maps to patients’ receipt of resources, and evaluate which generic services
are used across different providers, regions and the context of different models of
specialist palliative care.

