#### Predictors collected from clinicians

In both the development and validation phases, clinicians will record demographic,
clinical and episode start administrative data. Episode end data will be collected
at the end of each episode of care. Casemix data include phase of illness (stable,
unstable, deteriorating, dying), functional status (measured by Australia-modified
Karnofsky Performance Status (AKPS)), dependency (Modified Barthel Index), problem
severity (Integrated Palliative care Outcome Scale—IPOS staff version) and
caregiver needs (table 2). The measures are
available directly from phase of illness (www.pcoc.org.au), AKPS,^40^ Modified Barthel Index^41^ and IPOS (www.pos-pal.org), respectively. Phase of illness will be assessed
daily for people receiving inpatient care and at each face-to-face contact basis
for those receiving community-based care. Other variables including AKPS, Modified
Barthel Index, IPOS staff (and caregiver needs when feasible) will be collected at
the start of episode, end of episode and at change of phase of illness.

**Table 2 T2:** Data from clinicians in both development phase and validation phase

Type of data	Proposed cost predictors
Demographic data	Age
	Gender
	Postcode
	Ethnicity
	Marital status
	Living circumstances
	Need for interpreter
	Setting of care
Clinical data	Primary diagnosis
	Secondary diagnoses
	Comorbidities
Episode start and end data	Episode start date
	Episode end date
	Endpoint of episode (discharged or died).
	Discharge destination, if discharged
Key casemix	Phase of illness at start of episode
	Functional status (AKPS)
	Dependency (Modified Barthel Index)
	Problem severity (IPOS staff version)
	Family/caregiver needs

AKPS, Australia-modified Karnofsky Performance Status; IPOS, Integrated
Palliative care Outcome Scale.

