#### Predictors collected from patients and family caregivers

Variables (table 3) will be collected in
the validation phase from patients/caregivers using face-to-face/telephone
contacts and postal questionnaires according to their preferences.
IPOS patient version and Distress Thermometer will be collected from
patients at the start of episode, at change of phase of illness and at the end of
episode. Views on Care and Short-Form Health Survey V.2.0 (SF-12v2) will be
collected at the start and end of each episode of care. Selected questions
capturing experiences of integrated care^42^
will be collected at the end of episode only.

**Table 3 T3:** Predictors collected from patients and family caregivers in validation phase
only

Data collection from patients	Data collection from family caregivers
IPOS patient version	Basic demographic information
Distress Thermometer	Distress Thermometer
Views on Care	Two caregiver questions
SF-12v2*	Zarit six items
Patient experiences of integrated care	

*The measure could be completed by a family caregiver if the patient is
too unwell to complete.

SF -12v2, Short-Form Health Survey V.2.0.

All caregiver- reported measures will be collected at the start of episode, at
change of phase of illness and at the end of episode. Where phase length exceeds 4
weeks, data collected from patients (and caregivers) will be captured as a change
of phase. If the patient is transferred to an out-of-scope inpatient setting, we
will follow up with the patient when he or she gets home and
retrospectively collect minimum information about this episode of care.

If the patient is deceased, data such as SF-12v2 and Pall-CSRI will be collected
from the participating caregiver three months after death by postal
questionnaire, along with the bereavement support information and contacts. The
time between death and the postal questionnaire may influence caregivers’
willingness to share their views; shorter periods possibly being too upsetting to
contemplate involvement.^43^ There is mixed
evidence of the best time to make contact with potential participants for
follow-back surveys^44 45^ and 3–4
months post bereavement is considered acceptable by bereaved families.^30^

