### Sample size

In the development phase, based on standard recommendations for fitting multivariate
models, a minimum of 50+8×m (where m is the number of predictors) is required
to test the hypothesis that the population multiple correlation equals zero with a
power of 80%, alpha=5% and a medium effect size for the regression analysis
(R^2^=0.13).^46^ We estimated a
sample size of 450 episodes per setting (allowing for 25% incomplete episodes and up
to 10% of complete episodes being cost outliers with unusually high or low costs). A
total of 1350 patient episodes across settings is needed.

In the validation phase, again a minimum of 50+8×m (where m is the number of
predictors) is required to test the hypothesis that the population multiple
correlation equals zero with a power of 80%, alpha=5% and a medium effect size
for the regression analysis (R^2^=0.13).^46^ In phase II, the number of predictors reflects the casemix variables,
and needs to be clinically relevant^47^ to
ensure a meaningful casemix classification. We expect the final casemix
classification to contain 5–8 casemix variables, based on the Australian
experience.^13^ We have estimated that data
from 114 (50+(8×8)) episodes of care per setting (hospice, hospital,
community) are needed. Assuming an average of three episodes per participant^15^ in this longitudinal phase, this represents at
least 38 participants per setting. Allowing for 50% attrition, we estimate needing a
total of 228 participants, which will provide about 684 patient episodes. The sample
size will be recalculated and inflated using the design effect based on intraclass
correlation which will be estimated through interim analyses. A total of 300
participants across settings is needed, including extra 25% participants allowing for
intraclass correlation.

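### For the patient-versus-staff IPOS pair the plan names only correlation, which leaves a systematic scoring difference unassessed and may not compare across casemix classes

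*Protocol article*

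**What the plan says.** Under Development versus validation, the article sets patient-reported problem severity against professional-reported problem severity. The patient side is felt "need collected in validation phase only (as measured by the patient-reported IPOS"). The professional side is normative need, "as measured by the clinician-reported IPOS, phase of illness, AKPS), by reporting" "correlation across levels of complexity and across conditions". The next sentence adds an assessment of how "professional-reported measures relate to patient-reported outcomes across different" levels of complexity, meaning casemix classes, and names no statistic for it. The stated purpose is to determine "optimal outcome measures and quality indicators".

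Two other sections bear on this. Predictors collected from clinicians lists problem "severity (Integrated Palliative care Outcome Scale—IPOS staff version") among the key casemix data in both phases, collected at episode start, change of phase and episode end. Predictors collected from patients and family caregivers says "IPOS patient version and Distress Thermometer will be collected from" patients at the same three kinds of time point, in the validation phase only.

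The article names no mean difference, limits of agreement, intraclass correlation for agreement, or kappa for this comparison.

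**The concern.** Patient IPOS and staff IPOS can be compared in level as well as in rank. A correlation coefficient does not change when one rater's scores are shifted by a constant or stretched by a positive factor. A high coefficient is therefore compatible with staff scoring consistently below, or above, the patients they rate.

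This matters because phase I uses clinician data only, so problem severity enters the development work as staff see it. The validation phase is the first point at which patient IPOS is available, and this is the only patient-versus-staff IPOS comparison that the article describes. If its result guides the choice of outcome measures and quality indicators, a high correlation could support the staff version while a systematic difference goes unseen.

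A second, conditional point concerns reporting correlation by level of complexity. If problem severity turns out to be one of the variables that define the classes, the spread of staff scores within a class will be narrower than overall. Correlation falls with spread even when rating quality is constant.

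**Working it through.** The article gives no sample size, target or assumed correlation for this comparison, so there is no figure to reproduce. The values of r, the shift and the within-class spread below are all assumptions.

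**1. Effect of a constant shift.** Let both versions have SD 1 and correlation r, and let staff score d SD below patients. Pearson's r does not depend on d. Lin's concordance is 2r / (2 + d²).

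| r | d | Pearson r | Lin's concordance |
|---|---|---|---|
| 0.80 | 0.25 | 0.80 | 1.60/2.0625 = 0.78 |
| 0.80 | 0.50 | 0.80 | 1.60/2.25 = 0.71 |
| 0.80 | 1.00 | 0.80 | 1.60/3 = 0.53 |
| 0.60 | 0.25 | 0.60 | 1.20/2.0625 = 0.58 |
| 0.60 | 0.50 | 0.60 | 1.20/2.25 = 0.53 |
| 0.60 | 1.00 | 0.60 | 1.20/3 = 0.40 |

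A simulation of 200,000 pairs agrees. At r = 0.70, shifts of 0, 0.5 and 1.0 SD leave Pearson at 0.70, while concordance goes from 0.70 to 0.62 to 0.47. The mean difference reads 0, −0.50 and −1.00. At r = 0.90 with a 1.0 SD shift, concordance is 0.60; halving the staff spread as well takes it to 0.40, with Pearson still 0.90.

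**2. Effect of narrower spread within a class.** Let r = 0.80 overall, with no shift. Write patient score = 0.8 × staff score + error, with error variance 1 − 0.64 = 0.36. Suppose a class centred at the overall mean has staff-score SD u.

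- Pearson r = 0.8u / √(0.64u² + 0.36)
- Lin's concordance = 2(0.8u²) / (u² + 0.64u² + 0.36)
- SD of the differences = √(0.04u² + 0.36); the limits of agreement lie 1.96 times this either side of the mean difference

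| u | Pearson r | Lin's concordance | Limits of agreement (± SD units) |
|---|---|---|---|
| 1 | 0.80 | 0.80 | 1.24 |
| 0.5 | 0.4/√0.52 = 0.55 | 0.4/0.77 = 0.52 | 1.96 × √0.37 = 1.19 |
| 0.25 | 0.2/√0.40 = 0.32 | 0.1/0.4625 = 0.22 | 1.96 × √0.3625 = 1.18 |

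Concordance is as sensitive to spread as correlation is, so replacing one with the other by class would not help. The limits of agreement barely move.

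The mean difference by class needs one caution. If staff IPOS helps form the class, regression to the mean gives an expected staff-minus-patient difference of (1 − 0.8) × m in a class whose mean staff score is m SD from the overall mean. That is 0.20 SD at m = 1, with no true bias.

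**3. Can the planned data show a difference?** The Sample size section needs data "from 114 (50+(8×8)) episodes of care per setting (hospice, hospital", community), at three episodes per participant, or 38 participants. With one pair per episode and independent pairs, the mean difference detectable with 80% power at two-sided 5% is (1.96 + 0.84)/√114 = 0.26 SD of the differences. If a participant's three episodes were fully redundant, 38 would replace 114, giving 2.80/√38 = 0.45. The truth lies between these, before any loss of unpaired assessments.

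**The case against.** The strongest reply is that correlation answers what the article asks. The text sets out to compare two views of need and to see how the measures relate, and a correlation addresses the second. A reader might infer that the analysis fails its own stated question. The documents do not support that, because staff under-scoring or over-scoring is nowhere posed as the question. What remains is narrower: a comparison of two versions of one scale is incomplete if it ignores level.

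Two of the three professional measures, phase of illness and AKPS, share no scale with patient IPOS. Association is the natural summary for them. This stands, and the point is confined to the IPOS pair.

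A reader might also infer that a staff shift would put patients in lower severity bands. The article defines no IPOS bands. It takes problem severity from staff IPOS in both phases, so a uniform staff shift would move the tree's cut points with it and leave class membership unchanged. Nothing in the text plans to put patient scores through cut points derived from staff scores.

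Nor is it established that the range is restricted within classes. The classes are not yet built, and the candidate criteria include phase, function, age and model of care as well as problem severity. Diagnosis groups carry no such restriction by design. The comparability point is therefore conditional.

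Finally, a fuller analysis plan may add agreement measures, and the sentence on casemix classes names no statistic. That is possible, but the article does choose a statistic for the comparison, and that choice can be commented on.

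**Conclusion.** The point holds in a limited form. For patient versus staff IPOS, correlation is the only statistic the article names. By its nature it cannot reveal a systematic difference between the two raters. Comparability across casemix classes is also doubtful if problem severity helps define them.

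The document gives no basis for the size of any such difference. The illustrations rest on assumed correlations of 0.60 to 0.90 and assumed shifts of up to 1 SD. They show what correlation would miss, not what will be found.

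The comparison is secondary. It is not one of the two specific objectives, and it drives neither the cost model nor the sample size. The change is worth making because it is cheap and because the result is meant to inform the choice of measures and indicators.

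**What to change.** For patient versus staff IPOS, add the paired mean difference with limits of agreement as the lead summary, overall and by casemix class and diagnosis. Intervals should allow for repeated episodes within participants, for example through a mixed model or a participant-level bootstrap. If staff IPOS helps define the classes, say that by-class differences will include some regression to the mean.

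State a window for pairing the two assessments. The time points match in kind, but patient data are also collected when a phase exceeds 4 weeks, with no staff counterpart stated. Patient questionnaires may also arrive by post.

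Report an absolute-agreement ICC (or Lin's concordance) for the total score and weighted kappa per item as overall secondary summaries only, since they also depend on spread or prevalence. Keep correlation for phase of illness and AKPS against patient IPOS.

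The cost is a few sentences in the analysis section and a little more analysis work. Both IPOS versions are already collected, so no new data are needed.

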### Ethical considerations

The study protocol and documents (eg, the participant information sheet, consent and
declaration form) have been approved by the NHS Health Research Authority
London—Camberwell St Giles Research Ethics committee (15/LO/0887) for the
development phase, and NHS Health Research Authority London—Bromley Research
Ethics committee (16/LO/1021) for the validation phase.

All eligible participants are fully informed before consent is sought by
the local research team or research nurses or project research team through
the information sheets and verbal explanation on the aims and methods of the study
and procedures that might be involved. Participants can withdraw at any time up to
analysis of their data, without giving any reason. It is possible that participants
may become distressed or raise issues during this study which raise concerns or
warrant a change in their medical management, but we do not expect the questionnaires
will themselves cause distress so much as uncover pre-existing distress which has not
been acknowledged or recognised. Should this be the case, then our distress protocol
will be followed. We anticipate distress will be infrequent, given the general nature
of the questionnaires. It is likely that any distress will reflect advanced disease
and experiences of care, and not the questionnaires themselves. All of the study team
members have completed Good Clinical Practice training, and specific training on
addressing distress in palliative care.

Our existing Patient/Public Advisory Group and extended Consumer Panel have been and
will continue to be consulted throughout the study to ensure that the study is
carried out in an ethical and respectful way, and has the highest possible relevance
and benefit to patients and families. A Project Steering Committee meets once every
six months to monitor recruitment, review the detailed progress of the study and make
recommendations for overall direction and strategy.

### Dissemination

This study will lead to patient benefit through improved matching of resources to
needs at individual patient-level and will better enable the NHS to deliver
high-quality, patient-centred palliative care in last year of life. The results of
the study will be published in peer-reviewed publications and will also be presented
at national and international conferences.
